## Abstract

Microvascular angina is caused by cardiac small vessel disease, and dysregulation of the endothelin system is implicated. The minor G allele of the non-coding single nucleotide polymorphism (SNP) rs9349379 enhances expression of the endothelin 1 gene in human vascular cells, increasing circulating concentrations of ET-1. The prevalence of this allele is higher in patients with ischemic heart disease. Zibotentan is a potent, selective inhibitor of the ET_A_ receptor. We have identified zibotentan as a potential disease-modifying therapy for patients with microvascular angina.

**Methods:**

We will assess the efficacy and safety of adjunctive treatment with oral zibotentan (10 mg daily) in patients with microvascular angina and assess whether rs9349379 (minor G allele; population prevalence ~36%) acts as a theragnostic biomarker of the response to treatment with zibotentan.

The PRIZE trial is a prospective, randomized, double-blind, placebo-controlled, sequential cross-over trial. The study population will be enriched to ensure a G-allele frequency of 50% for the rs9349379 SNP. The participants will receive a single-blind placebo run-in followed by treatment with either 10 mg of zibotentan daily for 12 weeks then placebo for 12 weeks, or vice versa, in random order. The primary outcome is treadmill exercise duration using the Bruce protocol. The primary analysis will assess the within-subject difference in exercise duration following treatment with zibotentan versus placebo.

**Conclusion:**

PRIZE invokes precision medicine in microvascular angina. Should our hypotheses be confirmed, this developmental trial will inform the rationale and design for undertaking a larger multicenter trial.

## Background

### Microvascular angina

The term angina pectoris is derived from Latin, meaning “strangling of the chest”.^1^ Angina is a consequence of myocardial ischemia caused by an imbalance between myocardial blood supply and oxygen demand.^2^ Classically the management of patients with angina pectoris focuses on detection and treatment of flow-limiting epicardial coronary artery disease (CAD).^3^ However, fewer than half of patients with suspected angina have evidence of obstructive CAD on coronary angiography.^4^^,^^5^ Many patients with “normal” coronary angiography have signs, symptoms and investigations in-keeping with myocardial ischemia –this is termed ischemia with non-obstructive coronary artery disease (INOCA).^6^

INOCA is a heterogeneous group of conditions, including disorders of coronary anatomy, endothelial function and vasoreactivity.^7^ A growing body of evidence supports the differentiation of this group into distinct disease endotypes—the most common being microvascular angina and epicardial coronary vasospasm—that are amenable to stratified medicine.^3^^,^^8^

Microvascular angina is caused by coronary microvascular dysfunction. The Coronary Vasomotion Disorders International Study (COVADIS) Group define microvascular angina as symptoms of myocardial ischemia with proven coronary microvascular dysfunction (e.g. index of microcirculatory resistance (IMR) ≥25, coronary flow reserve (CFR) <2.0 or abnormal microvascular constriction during acetylcholine infusion), with unobstructed epicardial coronary arteries. (Table I).^9^

**Table I t0005:** Coronary Vasomotion Disorders International Study (COVADIS) clinical criteria for the diagnosis of microvascular angina

COVADIS criteria for microvascular angina	
1. Symptoms of myocardial ischemia	• Effort and/or rest angina • Angina equivalents (i.e. shortness of breath)
2. Absence of obstructive CAD (>50% diameter reduction and/or FFR <0.80) by either:	• CT coronary angiography (CTCA) • Invasive coronary angiography
3. Objective evidence of myocardial ischemia	• Ischemic ECG changes during an episode of chest pain • Stress-induced chest pain and/or ischemic ECG changes in the presence of transient/reversible abnormal myocardial perfusion and/or wall motion abnormality
4. Evidence of impaired coronary microvascular function	• Impaired coronary flow reserve (cut-off values depending on methodology use between ≤2.0 and ≤ 2.5) • Coronary microvascular spasm, defined as reproduction of symptoms, ischemic ECG shifts but no epicardial spasm during acetylcholine testing. • Abnormal coronary microvascular resistance indices (e.g. IMR >25, HMR ≥2.5 mm Hg·cm-1·s)^69^ • Coronary slow flow phenomenon

The pathogenesis of microvascular angina is multi-factorial and incompletely understood. It may involve structural and/or functional abnormalities of the microvasculature. Standard invasive coronary angiography lacks the spatial resolution to image the microcirculation directly.^10^ However, microvascular remodeling, with decreased luminal size and rarefaction (loss of capillaries) is implicated.^11^ Functional microvascular angina involves enhanced vasoconstriction and/or impaired coronary vasodilatation in response to physiological (e.g. exercise) or pharmacological e.g. acetylcholine, adenosine, stimuli of the coronary microvasculature, with endothelium-dependent and independent mechanisms being demonstrated.^12^

### Zibotentan

Endothelin-1 (ET-1) is a small peptide, produced primarily in the endothelium that is a potent constrictor of human blood vessels, and importantly is the most potent vasocontrict0r of the coronary arteries.13., 14., 15., 16. ET-1 is mediated by two receptors: ET_A_ and ET_B_. ET_A_ activation by ET-1 mediates coronary vasoconstriction.17., 18., 19.

Microvascular angina is associated with elevated circulating concentrations of ET-1 and prolonged exposure to ‘excess’ endothelin has harmful effects on small vessel function.^20^^,^^21^ Additionally, ET-1 mediates enhanced vasoconstriction in the peripheral arterioles of patients with microvascular angina compared to control subjects.^22^

Two trials of ET-1 receptor antagonists in patients with microvascular angina reported favorable, preliminary results (Reriani NCT00271492; Johnson NCT00738049). However, these trials were limited in size and unfortunately both atrasentan (hormone-refractory prostate cancer) and darusentan (resistant hypertension) were subsequently discontinued following neutral results from phase III trials relating to their primary indications, thus stopping any further investigation of their potential application in microvascular angina.^23^^,^^24^

There are theoretical benefits to selective ET_A_ receptor antagonism in cardiovascular disease, given that non-selective ET_A_ and ET_B_ receptor antagonists in heart failure cause deleterious fluid retention and adverse outcomes. Supportive evidence of ET_A_ selective antagonism can be drawn from studies in the population with heart failure and preserved ejection fraction (HFpEF). The natural history of these conditions is linked with microvascular angina reflecting chronic myocardial ischemia that may lead to HFpEF in the longer term.^25^ A double-blind, placebo-controlled, randomized controlled trial of sitaxentan in patients with HFpEF disclosed improvements in exercise tolerance conferred by this ET_A_ receptor antagonist.^26^

Zibotentan is a potent inhibitor of the ET_A_ receptor with no “off-target” binding to the ET_B_ receptor.^27^ We have identified zibotentan as a potential disease-modifying therapy for patients suffering from microvascular angina; however, it has not been used before in this patient group and is currently unlicensed. Zibotentan was initially developed as a possible treatment for cancer, but it did not improve survival in this group of patients.^28^ With the support of the AstraZeneca Open Innovation program, we have developed a clinical pathway for repurposing zibotentan as a novel treatment for patients with microvascular angina. The safety, pharmacokinetics (PK), pharmacodynamics (PD) and efficacy of orally administered zibotentan have been examined in 20 Phase I studies, 4 Phase II studies and 3 Phase III studies.^29^

The dose being used in this study is 10 mg once daily (having been previously studied at doses up to 240 mg in oncology studies) to achieve adequate target coverage over a 24-hour period, whilst minimizing side effects relating to ‘target engagement’ which include headache, nasal congestion/rhinitis, nausea and/or vomiting, and peripheral edema.^27^^,^^30^ Importantly, zibotentan has been tested ex vivo at these concentrations and has been shown to fully reverse an established ET-1 vasoconstriction, indicative of efficacy in conditions associated with vasospasm.^31^ Clearance of zibotentan is reduced in patients with hepatic or renal impairment.^30^ Zibotentan carries a risk of fetal toxicity and a theoretical risk of transfer via semen or breast milk.^29^ Clinical risk in PRIZE will be mitigated by the exclusion of patients with a medical diagnosis that is associated with toxicity and specific guidance regarding women of child-bearing potential (WoCBP) and their partners. (Table II).

**Table II t0010:** Exclusion criteria.

Exclusion criteria
1. Exercise tolerance >540 seconds in men and> 430 seconds in women during Full Bruce protocol or, lack of anginal symptoms and/or ST-segment depression (≥0.1 mV) limiting exercise.
2. Non-cardiovascular exercise-limiting problem e.g. morbid (or severe) obesity (BMI ≥40.0 kg/m^2^)
3. Genotype not available
4. Women who are pregnant, breast-feeding or of child-bearing potential (WoCBP) without a negative pregnancy test
5. Men who are sexually active with a WoCBP who are unwilling to highly effective methods of contraception for the duration of study treatment and for 14 weeks after the last dose of study drug.
6. Heart failure (New York Heart Association Grade ≥ II, i.e. mild symptoms and slight limitation during ordinary activity)
7. Recent (<3 months) myocardial infarction
8. A history of epilepsy, other CNS adverse events, neurologic symptoms or signs consistent with spinal cord compression or CNS metastases.
9. Moderate or more severe renal impairment (GFR <45 mL/min)
10. Liver disease with a Child-Pugh score of A (5–6 points) or higher
11. Participation in another intervention study involving a drug within the past 90 days

### Precision medicine in microvascular angina

The chronic elevation of circulating ET-1 in microvascular angina may be influenced by genetic factors. A gene variant of interest is rs9349379—this is a common non-coding single-nucleotide polymorphism (SNP) in the third intron of the protein-coding PHACTR1 gene on chromosome 6.^32^ This SNP regulates expression of the Endothelin 1 (EDN1) gene in human vascular cells which encodes the ET-1 protein. The minor G allele of this SNP (population prevalence ~36%) is associated with significantly increased circulating concentrations of ET-1.^33^

Emerging evidence from our laboratory (BHF CorMicA ClinicalTrials.gov: NCT03193294) indicates the prevalence of this SNP may be more common in patients with microvascular angina than is observed in age- and sex-matched controls. Patients with the rs9349379 G allele had higher serum ET-1 and over double the odds of coronary microvascular dysfunction. Additionally, subjects were more likely to have impaired myocardial perfusion and reduced exercise tolerance.^31^

### Hypothesis

Our hypothesis is that the ET_A_ antagonist, zibotentan, will be an effective treatment for patients with microvascular angina. We further hypothesize that the SNP regulator of EDN1 gene expression, rs9349379 (minor G allele), will act as a novel genomic theragnostic biomarker that associates with treatment response in this patient group. (Figure 1).

**Figure 1 f0005:**
[figure not shown]
Summary of the rationale for treatment with an ET_A_ antagonist in microvascular angina and for rs9349379 as theragnostic biomarker.

### Aims

1.To assess the efficacy of adjunctive treatment with zibotentan in patients with microvascular angina.2.To explore the mechanisms of any beneficial effects of zibotentan in microvascular angina.3.To assess genetic and clinical biomarkers for baseline patient characteristics and treatment response.4.To determine rates and severity of adverse events associated with zibotentan and evaluate its safety in a non-oncology population5.To explore the feasibility of the personalized medicine strategy in an ischemic heart disease population.

### Study design

The PRIZE trial has a prospective, randomized, double-blind, placebo-controlled, sequential cross-over design. The study population will be enriched to ensure the G-allele frequency of the rs9349379 SNP is at least 50%. Participants will receive a single-blind run-in with placebo followed by double-blind treatment with either 10 mg of zibotentan daily for 12 weeks then placebo for 12 weeks, or vice versa, in random order. The trial is designed to assess the superiority of the addition of oral zibotentan to guideline-indicated therapy as compared with placebo and guideline-indicated treatment for patients with microvascular angina. (Figure 2).

**Figure 2 f0010:**
[figure not shown]
Schematic study design: flow diagram. Abbreviations: Blood tests (B), Clinical review (C), Exercise tolerance test (ETT; Bruce protocol), Genomic blood test (GB), Questionnaires (Q), Stress perfusion cardiac magnetic resonance imaging (spCMR; optional sub-study), Pharmacokinetic and pharmacodynamic sampling (PK/PD).

### Patient identification

Patients will be identified from clinical databases, clinics and clinical procedure lists. The clinical pathways include but are not limited to: (1) out-patient clinics including patients with a diagnosis of microvascular angina; (2) diagnostic stress tests, e.g. stress perfusion magnetic resonance imaging (MRI), stress echocardiography, stress nuclear imaging with PET or SPECT or an exercise ECG leading to a diagnosis of microvascular angina; (3) invasive or CT coronary angiography.

### Eligibility criteria

The inclusion criteria are: (1) age >18 years old; (2) microvascular angina; (3) able to comply with study procedures; (4) able to provide written informed consent.

In PRIZE, we define microvascular angina as per the COVADIS guideline (Table I). The criteria are:1.Symptoms of myocardial ischemia.2.Absence of obstructive CAD (>50% diameter reduction or FFR <0.80) by either CT or invasive coronary angiography.3.Objective evidence of myocardial ischemia.4.Evidence of impaired coronary microvascular function.

In order to participate in this trial, the patient should have a diagnosis of microvascular angina (probable or definite). Probable microvascular angina is defined as having 3 of the 4 COVADIS criteria. Definite microvascular angina requires all 4 COVADIS criteria. Participants in this trial should also fulfill criteria 1 & 2. This diagnostic classification is endorsed by the European Society of Cardiology practice guidelines (August 2019).^3^

The exclusion criteria are listed in Table II

### Recruitment

Three hundred fifty-six patients will be enrolled following written informed consent. Those eligible on clinical grounds will undergo genotype blood testing. All those with the GG genotype will continue to the run-in phase, whereas only a proportion of those with the AA and AG genotypes will proceed. This will boost the relative frequency of the G genotypes in the study population, with the objective of achieving 50% G allele frequency. If a consented patient is found to be ineligible for the run-in/treatment phase of the randomized trial, they will remain included in the study population, including consent for long term follow up using linkage of electronic government and patient records (EPR).

Following genotyping and enrichment of the study population with the minor G allele for the rs9349379 SNP we anticipate enrolling at least 144 patients into the run-in phase of the study. Allowing for up to 30% drop-out during run-in, at least 100 participants will proceed to randomization.

### Genotyping

Genomic DNA will be extracted from a peripheral blood sample (EDTA containing tube taken during Visit 1). A Sanger sequencing approach, using the forward primer “F_GTGCAATTCTCCAAGGCTCC” and the reverse primer “R_TTTAAAACTCAGCTCGTGGAAAA”, will be used to sequence part of intron 3 of the PHACTR1 gene to determine the genotype of the rs9349379 SNP.

### Medical optimization

Since microvascular angina is a chronic condition, most patients will already be established on maintenance drug therapy. In some cases, cardiovascular risk factors, including blood pressure and lipids, may not be optimally managed. To accurately assess the efficacy of zibotentan, we will first ensure that patients recruited to the study are being managed with guideline-directed medical therapy as per contemporary practice guidelines and local standards of care. This process includes informed consent (Visit 1) through to treatment run-in (Visit 2). The medical optimization period is intended to identify patients with unstable symptoms or uncontrolled cardiovascular risk factors. In affected cases, optimization of pharmacological and non-pharmacological treatments and will be carried out by clinical staff including clinical research nurses, study physicians and pharmacists, as clinically appropriate.

The clinical review and optimization process will follow a standard operating procedure (SOP), in line with contemporary clinical practice guidelines, notably those issued by the European Society of Cardiology.^3^ For logistical reasons, this optimization phase is limited to 6 weeks. If angina drug therapy is changed, then a period of 4 weeks will follow before proceeding into the treatment run-in phase. Following optimization, angina therapy will remain the same from entry into the treatment run-in period (Visit 2) and thereafter.

## Outcomes

### Primary outcome

The primary outcome for our study is the treadmill exercise time (seconds) using the full Bruce exercise tolerance test protocol.^34^ Exercise testing using the Bruce protocol is a standard of care in clinical cardiology and evidence-based for assessing functional capacity, susceptibility to effort-related anginal symptoms and ischemia in patients with stable angina.^35^ Treadmill exercise time (s) is a reproducible outcome measure35., 36., 37., 38., 39., 40., 41., 42. with an approximately 10% test-retest variability.^36^^,^^42^ In a study of repeated exercise testing in older women the intra-class correlation coefficient of exercise duration was 0.88.^38^ In a clinical trial involving 33 patients with microvascular angina, there was 100% compliance with serial exercise tests (n = 4 per subject). Patient and Public Involvement (PPI) in the design of this study provided encouraging feedback to the effect that exercise tests are generally well tolerated. Treadmill exercise testing is also accepted by regulators, such as the Federal Drug Administration, for assessing the efficacy of angina medications.

### Secondary outcomes

The pre-specified secondary outcomes are described in Table III.

**Table III t0015:** Secondary outcomes.

Secondary outcomes	
Exercise test	• Time (s) to 1 mV ST depression
	• Maximum ST-segment deviation (mV)
	• Time (s) to 75% of max age-related heart rate during exercise
	• Metabolic equivalent (METs)
	• The DUKE Score^70^
Health Status Questionnaires	• Seattle Angina Questionnaire (SAQ)^43^
	• Illness perception • (Brief IPQ)^48^
	• Anxiety/depression • (PHQ4)^50^
	• Treatment satisfaction • (TSQM)^49^
	• EQ-5D-5L^47^
Safety	• Frequency and severity of severe adverse events (SAEs)
Feasibility	• Participant withdrawal rate
Efficacy	• Pharmacokinetics • Pharmacodynamics
Exploratory endpoints/outcomes	
Patient-Reported Outcome Measures (PROMS)	• Angina diary

The primary and secondary outcomes, and the MRI sub-study, are intended to provide surrogate outcome information that is mechanistically linked to the pathogenesis of microvascular angina. Accordingly, the results of our precision medicine trial should be informative about the potential role for zibotentan as a disease-modifying therapy for microvascular angina.

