## Statistical considerations

### Sample size calculation

The primary outcome is the treadmill exercise time (seconds). A 30-second difference in exercise duration is considered clinically significant.51., 52., 53. The standard deviation of the difference between two exercise test measurements is assumed to be 85 seconds.^51^ To achieve 80% power to detect a mean difference of 30s between treatments in a 2 × 2 crossover design and a level of significance of 0.05 (alpha error) requires complete data in 65 subjects. At least 100 subjects will be randomized to allow for data quality issues and loss to follow-up. Considering the clinical optimization (visit 1–2) and single-blind placebo run-in (visits 2 and 3), we anticipate a drop-out of up to 30% may occur (n = 42), meaning we will aim to have 144 begin the run-in phase of the trial to randomize 100.

Pre-specified subgroup analyses are intended for sex, a history of vasospastic angina, and the duration of symptoms.

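### Table III sets a secondary ST-segment outcome at 1 mV, ten times the 0.1 mV threshold in Table II; most likely a unit or decimal slip

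*Protocol article*

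**What the plan says.** Two tables of the Protocol article give an ST-depression threshold in millivolts.

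- **Outcomes, Secondary outcomes, Table III.** Under the exercise-test heading, one outcome is "Time (s) to 1 mV ST depression". The next row is maximum ST-segment deviation, also in mV but with no threshold.
- **Zibotentan, Table II, exclusion criterion 1.** Patients are excluded if they exercise beyond a sex-specific limit on the full Bruce protocol (540 s for men, 430 s for women), or for "lack of anginal symptoms and/or ST-segment depression (≥0.1 mV) limiting exercise".

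The Primary outcome section names the full Bruce protocol as the test for the primary endpoint. Both thresholds therefore refer to the same kind of test. The article states no other ST threshold in mV and gives no reason for the outcome threshold to exceed the eligibility threshold.

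**The concern.** A time-to-threshold outcome is informative only if a fair share of participants reach the threshold. Table II treats 0.1 mV as the level of ST depression that counts as a limiting sign on the treadmill. Table III asks for ten times as much before the outcome occurs. If the endpoint were derived literally, most tests would end before the event in both treatment phases. There would then be little or nothing to compare between zibotentan and placebo on this outcome.

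This is not a detail that an article may leave to a fuller document. It is a stated numerical definition of a pre-specified outcome, and it sits badly with the article's own figure. If the intended value is 0.1 mV and the table stays as it is, one of two things follows. Either the outcome is derived at a level hardly anyone reaches, or the analysis uses a threshold that differs from the published one.

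**Working it through.** **Step 1. The contradiction itself.** The 1 mV is a definition, so no formula in the plan generates it. It can only be set against the other stated value:

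- Outcome threshold (Table III): 1 mV
- Eligibility threshold (Table II, criterion 1): 0.1 mV or more
- Ratio: 1 / 0.1 = 10

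This needs no assumption. At an assumed ECG calibration of 10 mm per mV, which the article does not state, 0.1 mV is 1 mm and 1 mV is 10 mm. That would explain the entry as mm written as mV. A lost decimal explains it equally well.

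**Step 2. How many participants would reach each threshold.** The article gives no distribution of peak ST depression, so one is assumed: lognormal with mean m from 0.10 to 0.30 mV and coefficient of variation (CV) of 0.5 or 1.0. With Φ the standard normal distribution function,

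- s = √ln(1 + CV²), which is 0.472 for CV 0.5 and 0.833 for CV 1.0
- μ = ln(m) − s²/2
- P(peak ≥ c) = 1 − Φ((ln c − μ)/s)

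Worked example for m = 0.30 and CV = 1.0: μ = −1.204 − 0.347 = −1.551. For c = 1 mV, (0 + 1.551)/0.833 = 1.86, so P = 0.031. For c = 0.1 mV, (−2.303 + 1.551)/0.833 = −0.90, so P = 0.817.

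| Mean (mV) | CV | Reach 1 mV, per 100 | Reach 0.1 mV, per 100 |
|---|---|---|---|
| 0.10 | 0.5 | <0.001 | 41 |
| 0.10 | 1.0 | 0.07 | 34 |
| 0.15 | 0.5 | 0.001 | 73 |
| 0.15 | 1.0 | 0.35 | 53 |
| 0.20 | 0.5 | 0.01 | 89 |
| 0.20 | 1.0 | 0.94 | 66 |
| 0.30 | 0.5 | 0.27 | 98 |
| 0.30 | 1.0 | 3.1 | 82 |

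The Sample size calculation section says "At least 100 subjects will be randomized to allow for data quality issues and loss to follow-up". With 100 participants tested, the expected number reaching 1 mV in a treatment phase is therefore between about 0 and 3, and below 1 in seven of the eight cases.

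**Step 3. Whether anything else depends on this value.** The sample size uses a 30 s difference, an SD of 85 s, 80% power and alpha 0.05 (taken as two-sided). The normal approximation is ((1.960 + 0.842) × 85/30)² = 63.0, rounded up to 64. With the noncentral t distribution, power is 0.794 at 64 and 0.800 at 65. The stated 65 reproduces, and no ST threshold enters it. Maximum ST-segment deviation has no threshold and is also untouched.

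**The case against.** The strongest reply is that this is a misprint in a condensed article. The working definition would sit in the full protocol, the SAP and the exercise-test form, none of which is shown, and those may already say 0.1 mV. That stands as a limit on the consequence: the effect on the trial as conducted is unknown. It does not remove the error from the published outcome definition.

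A second reply is that an eligibility limit and an outcome event need not share a value, so the two tables do not strictly exclude each other. This also stands in part. A tenfold gap in the same unit on the same test, with no reason given, makes a slip very likely but does not prove one.

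A third is that 0.1 mV is no guarantee of an informative endpoint. On one natural reading of the and/or in criterion 1, a patient limited by angina alone can enter without ever reaching 0.1 mV. The illustration itself goes as low as 34 per 100 at 0.1 mV. Some censoring will therefore remain after correction, though far less than at 1 mV.

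A reader might also infer that the trial loses its main objective measure of ischaemia. The article does not support that. Table III sets no ranking among its outcomes. Maximum ST-segment deviation and the Duke score remain, and the MRI sub-study is planned to assess myocardial blood flow in 60 participants.

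**Conclusion.** The point holds as an inconsistent outcome definition of moderate severity. The factor of ten is exact and rests on the article alone. The practical effect, about 0 to 3 participants per 100 reaching 1 mV against about 34 to 98 per 100 at 0.1 mV, rests on the assumed lognormal distributions and should be quoted only with them. Over that range the outcome, read literally, would be nearly uninformative.

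It would be tempting to say that every test would be censored and that the comparison would have no power. The documents give no distribution of peak ST depression from which to establish that, and the upper end of the illustration is about 3 per 100, not zero. The damage is confined to one of the two ST-segment rows among the secondary outcomes.

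**What to change.** In Table III, replace 1 mV with 0.1 mV (1 mm) in the time-to-ST-depression row, so that it matches criterion 1 in Table II. Confirm that the full protocol, the SAP and the exercise-test form carry the same value and unit. If a threshold other than 0.1 mV was really intended, state it with its reason, so that the two tables are reconciled openly.

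The cost is one figure in one table plus a check of three documents. Design, sample size, eligibility and the other outcomes stay as they are. The correction should be made and dated before unblinded data are analysed, so that it cannot be read as a change prompted by the results.

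### Maximum ST-segment deviation is a peak over a test whose length is the primary outcome, so a true but modest reduction in ischemia can appear null or reversed

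*Protocol article*

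**What the plan says.** The Primary outcome section of the protocol article states: "The primary outcome for our study is the treadmill exercise time (seconds) using the full Bruce exercise tolerance test protocol". The Sample size calculation section adds that "A 30-second difference in exercise duration is considered clinically significant" and powers the trial on that difference. The Abstract says the comparison of zibotentan with placebo is within subject.

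Table III (Secondary outcomes) lists "Maximum ST-segment deviation (mV" with no time, stage or workload attached, so as written it is the largest value over the whole test. The same table lists time to an ST-depression threshold, "Time (s) to 75% of max age-related heart rate during exercise", METs and the Duke score. The text below it describes the primary outcome, the secondary outcomes and the MRI sub-study together as surrogate information with a mechanistic link to the disease.

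Table II, exclusion criterion 1, removes patients with a "lack of anginal symptoms and/or ST-segment depression (≥0.1 mV) limiting exercise". Those who enter are therefore people whose exercise is limited by angina, by ST depression, or by both.

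**The concern.** The Bruce test is incremental: workload rises as the test goes on. A maximum over the whole test therefore depends on how ischemic the heart is at a given workload and on how far the participant gets. The trial hypothesizes that zibotentan changes both, and their effects on the maximum go in opposite directions. Less ischemia at each workload lowers it; a longer test raises it.

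Participants are selected because angina or ST depression limits them, so many may stop near their own ischemic limit on either treatment. A drug that moves that limit later would leave the maximum about where it was. At stake is a secondary result that reads as no anti-ischemic effect, or as worsening, beside a longer exercise time, in a developmental trial meant to inform a larger one.

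**Working it through.** **Step 1: the plan's own figure.** Inputs from the Sample size calculation section: difference 30 s, SD of the difference 85 s, power 80%, alpha 0.05 (two-sided assumed).

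n = (85 × (1.960 + 0.842) / 30)² ≈ 63.0, so 64 by the normal approximation. With the noncentral t on n − 2 degrees of freedom, power is 0.794 at n = 64 and 0.800 at n = 65. The stated 65 complete subjects reproduces. No number in the plan is disputed; the 30 s serves below as the planned gain in exercise time.

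**Step 2: the outcome as a formula.** Let ST depression on placebo start at time t0, deepen linearly at b mV/s, and end at the stop T. On zibotentan, onset is delayed by d, the slope falls by a fraction r, and the stop is at T + g.

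- Difference in maxima = b(1 − r)(T + g − t0 − d) − b(T − t0)
- Difference at matched time T = b(1 − r)(T − t0 − d) − b(T − t0)

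Subtracting, the maximum exceeds the matched-time difference by b(1 − r)g. This term always acts against the drug and grows with the gain in exercise time. With the slope unchanged (r = 0), the difference in maxima is b(g − d): zero when the test lengthens by as much as onset is delayed, positive when it lengthens by more.

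**Step 3: numbers.** The curve is an assumption and is not in the documents: t0 = 150 s, T = 350 s, 0.15 mV at the stop, so b = 0.15/200 = 0.00075 mV/s. A 350 s stop lies below both entry ceilings in Table II (540 s for men, 430 s for women). With g = 30 s:

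| Assumed true effect | Difference in maxima (mV) | Difference at matched time (mV) |
|---|---|---|
| Onset 30 s later | 0.000 | −0.0225 |
| Onset 15 s later | +0.011 | −0.011 |
| Slope 10% lower | +0.005 | −0.015 |
| Onset 30 s later and slope 20% lower | −0.030 | −0.048 |

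First row: the zibotentan maximum is 0.00075 × (380 − 180) = 0.150 mV, the same as placebo; at 350 s it is 0.00075 × 170 = 0.1275 mV against 0.150 mV.

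**Step 4: a wider grid.** Take g of 30 or 60 s, d of 0, 15 or 30 s, and r of 0, 10% or 20%. Of the 18 combinations, 16 contain a true reduction at matched time. Among these 16 the difference in maxima is positive in 8, zero in 1 and negative in 7, and runs from −0.030 to +0.034 mV. In all 7 negative cases it is smaller in size than the matched-time difference. In the two combinations with no anti-ischemic effect the maximum rises by 0.023 and 0.045 mV from the longer test alone, and the matched-time difference is 0. These counts describe the grid and are not probabilities.

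**Step 5: a second assumed curve.** If onset is at 200 to 300 s and 0.1 mV is reached at 400 s, the slope is 0.1/200 = 0.0005 to 0.1/100 = 0.001 mV/s. Shifting curve and stop by 30 s lowers ST depression at matched time by 0.015 to 0.03 mV, again with no difference in maxima.

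**The case against.** **Companion outcomes.** Table III also has time to an ST-depression threshold, which is not tied to the end of the test and would pick up a delayed onset, and METs, which record workload. This limits the harm. The safeguard is weakened because the threshold is printed as 1 mV, whereas exclusion criterion 1 uses 0.1 mV. Taken literally, 1 mV would probably almost never be reached.

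**Role of the outcome.** A reader might infer that maximum ST deviation is the trial's test of ischemia. The article does not say so. Aim 2 names no outcome, the Pharmacodynamics section ties mechanism to circulating biomarkers, and the MRI sub-study addresses myocardial blood flow. This objection stands and keeps the point minor.

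**Assumed curves.** The exact zero arises because curve and stop are shifted by the same 30 s. Some participants will stop for angina rather than at a given ST level. This also stands: the effect is conditional, and with a strong enough drug effect the maximum still falls. What does not depend on the curve chosen is the direction of the distortion, provided ST depression deepens as exercise continues.

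**The SAP.** A matched reading could be specified in an analysis plan that is not shown, and Table III does not preclude it. But the outcome named in the article would still be the maximum, so the point concerns a definition rather than an omitted detail.

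**Conclusion.** The point holds for maximum ST-segment deviation. Under the assumed curves, a true reduction of about 0.01 to 0.02 mV at matched time can read as zero or slightly positive when the test is 30 s longer, and a reduction of 0.048 mV reads as 0.030 mV. This rests on workload rising through the test, ST depression deepening with it, and zibotentan lengthening exercise as hypothesized. The documents give no ST slopes, so the true size is unknown. Severity is minor: one secondary outcome, with the primary analysis unaffected.

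A reader might extend the point to time to 75% of age-related maximal heart rate. The documents do not support that. It is the time at which a fixed submaximal threshold is first crossed, so exercise after the crossing cannot change it, and it does not measure ischemia directly. Test length enters only through tests that stop before the threshold, and handling those is a censoring rule commonly left to the SAP. In a simulation with assumed heart-rate curves, 30 s more exercise and no drug effect on heart rate, the mean paired difference was 0.0 s without truncation, +0.7 s among those reaching the threshold in both tests, and +2.7 s if the others were set to the end of the test. None of these is in the direction of apparent worsening.

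**What to change.** In Table III, add ST-segment depression at matched exercise time within participant: the value at the last time point or Bruce stage reached in both the zibotentan and the placebo test, read blinded to treatment. Make this the between-treatment comparison of ST magnitude. Keep maximum ST deviation as a descriptive value and as an input to the Duke score. Leave the heart-rate outcome unchanged. Separately, reconcile the 1 mV threshold in Table III with the 0.1 mV in Table II.

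The cost is one added outcome definition and one extra reading from exercise tests already planned, with no new visit or participant. There are three downsides. Both tests must be in hand before the reading is made. The ECG must be available at the matched time or stage, which the article does not confirm. The comparison is uninformative where the shorter test ends before ST depression begins.
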